#### Outcome analyses

Detailed outcome measure analyses can be found in the predefined SAP; available on request to the Trial’s Office ([contact]). Briefly, RNFL will be measured immediately prior to treatment commencement (baseline measurement) and then at each of the onsite visits over the 24 months post-intervention (including unscheduled visits for suspected device failure). These measurements will be analysed using hierarchical repeated measures models, only the first 6 months of which will be used in the analysis of the primary outcome. The analysis will include all randomised patients, grouped according to the intervention to which they were assigned.

A random-effects structure will be used to handle repeated measures nested within one eye through time, with each eye nested within a participant. Analysing data from each eye, as opposed to the worst eye, will increase statistical efficiency.^46^ However, there are analysis inclusion criteria at the eye level, due to the possibility that some patients will have only one eye that meets the eligibility criteria (the study eye). In these instances, only measures taken from the study eye will be used in the analysis (eg, where there are non-IIH causes of disease within an eye or an IIH eye that does not meet the eligibility criteria; any measurements taken will not be analysed). Moreover, where data from each eye are analysed, it is imperative to handle the high correlation between eyes within individuals.^46^

Hierarchical models will be used to model both eyes, which are assumed to be nested within participants. These models will therefore have a fixed intercept and fixed effects for the progression of RNFL thickness through time (both with and without a treatment interaction), adjustments for covariates (including but not limited to stratification variables (see ‘Randomisation’ section)) and random effects for the effect of participant on the intercept (participant random intercepts) and the effect of eye within participant on the intercept and slope (eye within participant random intercept and slope). If this model does not fit the observed data satisfactorily, alternative models and explanatory variables (such as age, sex and treating centre) will be considered. The presence of a treatment effect will also be tested by a likelihood ratio test against a nested model with no treatment variable and otherwise identical model specification.

Other visual outcomes will be analysed in a similar way as they can be assumed to be continuous. For the analysis of global RNFL thickness, we acknowledge that loss of the ganglion cell layer (GCL) may cause a pseudo-reduction in RNFL. Therefore, in addition to the primary estimand detailed above, we aim to differentiate any reduction in RNFL owing to an improvement in disease following intervention from any reduction in RNFL owing to the loss of GCL. Therefore, we propose a supplementary estimand, which will be analogous to the analysis detailed above, with the key difference being that GCL will also be adjusted for through the joint modelling of both. This analysis will have the added benefit of allowing the ascertainment of whether the rate of GCL death is comparable between arms.

The major attributable complication rate between the DVSS and CSF shunting arms will be compared using a two-sample test for a difference in proportions.

Headache outcomes, including MHD will be analysed using multilevel negative binomial models with constant overdispersion parameter. These models will have fixed terms for the mean baseline value, the assessment times and treatment arm, with random intercepts to reflect the heterogeneity in baseline values and the serial correlation in repeated measures. Akin to the primary outcome, the presence of a treatment effect will again be tested by a likelihood ratio test against a nested model with no treatment variable and otherwise identical model specification.

All other outcomes, their intercurrent events of interest and estimands are given in the SAP.

Supplementary subgroup analyses may be performed by shunt type (LP vs VP CSF shunt) against DVSS, as appropriate.

There are no formal interim analyses with associated decision criteria. Instead, the independent data monitoring committee (DMC) will meet at least annually, and be presented with interim analyses, including safety and primary outcome data.^41^

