### Trial design

IIH Intervention is a two-arm, open-label, multicentre, randomised controlled phase IIb clinical trial with an integrated health economic evaluation. All recruitment centres are National Health Service (NHS) hospitals in the UK. The trial will compare CSF shunting with DVSS, the two most common interventions performed in the UK for patients who have confirmed IIH and are at risk of permanent visual loss due to papilloedema (figure 1).

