#### Economic evaluation

To assess the cost-effectiveness of DVSS compared with CSF shunting, a within-trial economic evaluation will be undertaken and will include both a cost-effectiveness analysis and a cost-utility analysis at 12 months. If the economic evaluation at 12 months reveals that DVSS is not dominated by CSF shunting (ie, it is not both more costly and less effective) then a decision-analytic model will be developed to enable an economic analysis over a longer time horizon. The model will be populated using trial data collected at 24 months, as well as data from other sources to extrapolate results over a lifetime horizon. The economic evaluation will be undertaken from a UK health system perspective.

For the cost-utility analysis, quality-adjusted life years (QALYs) will be measured using the EQ-5D-5L collected at baseline, 1 and 2 weeks immediately following the intervention and then at 1, 4, 6 and 12 months and at any unscheduled visit for revision/device failure.

Utility weights will be obtained by using the EQ-5D index tariff. Mean differences in EQ-5D between the trial arms will be estimated and presented with statistical tests of significance. Any imbalance in baseline utility will be adjusted. The within-trial cost-effectiveness analysis will use ‘major complications avoided’ as the outcome measure, assessed using the Clavien-Dindo grade III–V criteria for classification.^47^

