#### Adverse events and medical device deficiencies

Adverse events (AEs) will be reported in accordance with Clavien-Dindo classification^47^ and/or National Cancer Institute Common Terminology Criteria for Adverse Events, V.5.0.^48^ Definitions of different types of AEs and medical device deficiencies are listed in online supplemental appendix 6. The reporting period for AEs will be between consent until 360 days after initial trial intervention. In addition, any medical device deficiencies will be recorded up to 24 months post-trial intervention specifically related to the medical device allocated at randomisation. The investigator should assess the seriousness and causality (relatedness) of all AEs experienced by the participant (this should be documented in the source data) with reference to the protocol. This will include abnormal laboratory findings, which are reported as clinically significant. All AEs will be reported using the applicable electronic case report form (eCRF).

The investigator will exercise their clinical judgement in deciding whether an abnormal laboratory finding or other abnormal assessment is relevant. However, if in the opinion of the investigator, the frequency or severity of the event is greater than would be expected then it must be reported.

Participants receiving CSF shunting or DVSS as the primary trial intervention may require admission to hospital for appropriate medical intervention following development of some of the more severe known side effects of the intervention (online supplemental appendix 7). The following are regarded as expected serious AEs (SAEs) for the purpose of this study:

SAEs relating to CSF shunting unless the condition is life threatening or proves fatal.SAEs relating to DVSS unless the condition is life threatening or proves fatal.

Any death occurring during the reporting period, whether considered device-related or not, must be reported as an SAE within 24 hours of the local investigator becoming aware of the event. If a death is considered potentially related to either the CSF shunt or stent, then the cause of death will be investigated and reviewed by the trial management group (TMG), DMC and clinical team caring for the participant. Where the death is considered as potentially related to the DVSS intervention, entry of patients into the trial will be temporarily suspended until these investigations are complete.

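### The one between-arm complication test the article names counts only attributable events in an open-label trial, and its relation to the economic count of major complications is not stated

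*Protocol article*

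**What the plan says.** The protocol article, under Outcome analyses, sets the comparison: "The major attributable complication rate between the DVSS and CSF shunting arms will be compared using a two-sample test for a difference in proportions". It gives no severity grade for major and no definition of attributable.

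Trial design describes the masking: "IIH Intervention is a two-arm, open-label, multicentre, randomised controlled phase IIb clinical trial". Adverse events and medical device deficiencies says who judges cause: "The investigator should assess the seriousness and causality (relatedness) of all AEs experienced by the participant". The only further causality review described is for deaths possibly related to the shunt or stent, which go to the trial management group, the data monitoring committee and the clinical team. All adverse events are recorded on the eCRF, related or not, over a fixed window: "The reporting period for AEs will be between consent until 360 days after initial trial intervention". On grading, the section says "Adverse events (AEs) will be reported in accordance with Clavien-Dindo classification" and/or CTCAE version 5.0.

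Economic evaluation uses a count with a severity threshold and no stated attribution condition: "The within-trial cost-effectiveness analysis will use ‘major complications avoided’ as the outcome measure, assessed using the Clavien-Dindo grade III–V criteria for classification".

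**The concern.** Complications and revisions will weigh heavily in any choice between shunting and stenting. A test restricted to attributable events depends on a causal judgement for each event. In an open-label trial that judgement is made with the procedure known, unless some masked process is laid down elsewhere.

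The procedures also fail in different ways. Under Intervention failure the article names mechanical problems and infection for a shunt, and thrombosis or re-stenosis for a stent. The share of events called attributable could therefore differ by arm.

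Randomisation balances background events in expectation, so a comparison of all major complications needs no causal judgement. The filter brings one back in. If the economic count is unfiltered, the clinical and cost-effectiveness conclusions could also rest on different counts of harm, and the reader could not tell from the article.

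**Working it through.** The article gives no expected rate, alpha or power for the complication test, so there is no stated figure to reproduce. The calculation below only shows how far differential attribution could move the named test.

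**Inputs from the article**
- n = 40 per arm (Sample size).
- 14%: first-year stent revision rate in a single-centre series (Introduction).
- 71%: upper end of the reported range for shunt complications and revisions (Introduction).

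The two rates only anchor the range. Neither is a major-complication risk as this trial would define it.

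**Assumptions**
- Two-sided 5% test.
- Intermediate true risks of 30% and 50%.
- All attribution shares.
- Truly unrelated events are equally common in both arms. With equal total risks, a difference in shares is then misclassification.

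**Formulas.** Let p be the true proportion of participants with a major complication in an arm, and q the share of those counted as attributable. The proportion seen by the test is p × q. With equal true risks the spurious difference is p × (q1 − q2), which is zero when the shares are equal. The test statistic is z = (x1 − x2)/n ÷ √[p̄(1 − p̄) × 2/n], where p̄ = (x1 + x2)/(2n). The rejection probability is the exact sum of the two binomial probabilities over all pairs (x1, x2) with |z| > 1.96.

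**Equal true risks (any rejection is false)**

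| True risk | All counted | 95% v 85% attributed | 95% v 75% attributed |
|---|---|---|---|
| 14% | 5.4% | 6.0% (gap 1.4 points) | 7.4% (gap 2.8) |
| 30% | 4.8% | 6.0% (gap 3.0) | 9.3% (gap 6.0) |
| 50% | 5.7% | 8.0% (gap 5.0) | 15.6% (gap 10.0) |
| 71% | 4.9% | 10.0% (gap 7.1) | 26.0% (gap 14.2) |

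Example: at a true risk of 30%, 0.30 × 0.95 = 28.5% and 0.30 × 0.75 = 22.5%, a spurious gap of 6.0 points.

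**A true difference partly hidden**
- True 40% v 14%, all counted: power 76.5%.
- Same risks, with 75% and 95% attributed: 0.40 × 0.75 = 30.0% and 0.14 × 0.95 = 13.3%. The difference shrinks from 26 to 16.7 points and power falls to 45.0%.

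**The two descriptions of major complications side by side.** Outcome analyses gives an attribution condition and no grade. Economic evaluation gives a grade and no attribution condition. Two readings fit: one endpoint described in part each time, or two endpoints. Nothing in the article settles which.

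**The case against.** The strongest reply is that the article is a summary. Four stronger readings are tempting, and the document supports none of them.

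- *That this is the trial's only safety comparison.* The text names one test. Other safety, complication and revision outcomes are placed in supplemental appendix 5, and other estimands in the SAP; neither is shown. The data monitoring committee also sees interim safety data.
- *That the investigator's relatedness call decides what is attributable.* This is a reasonable inference, but no sentence links the two. A definition or an adjudication process may sit in the full protocol or SAP, and its absence here is not a finding.
- *That the trial will report two conflicting counts.* The two sections may describe one endpoint. If the economic count is unfiltered, an all-cause grade III–V count is already planned.
- *That events graded only by CTCAE drop out of the grade III–V count.* This is not shown. The and/or wording is compatible with Clavien-Dindo for procedural complications and CTCAE for other events, and the economic outcome itself calls for Clavien-Dindo grading.

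It is also fair to say that an attributable rate answers a legitimate question about the procedures, that the direction of any attribution bias is speculative, and that the shares used above have no source in the article. Small gaps matter little in a trial of this size: 8 v 6 events of 40 gives z = 0.05/0.085 = 0.59, p ≈ 0.56.

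What survives is stated text: the named test carries the filter, the trial is open-label, the only assessor described is the investigator, and the two sections are not tied together.

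**Conclusion.** The point holds in a limited form. The one between-arm complication test the article names depends on an attribution judgement that, as far as the article shows, is made by people who know the procedure. If attribution differs by arm, the test is biased, in a direction that cannot be known beforehand. The article also leaves open whether the economic outcome is the same endpoint.

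The size is illustrative. Under assumed 95% v 75% attribution, false rejection is about 7% to 26% over true risks of 14% to 71%. Under 95% v 85% it is 6% to 10%. Loss of power can be larger: from 76.5% to 45% for an assumed 40% v 14% with 75% and 95% attributed. At low event rates or small attribution gaps the effect is modest. The figures assume 40 per arm, a two-sided 5% test and background events equally common in both arms. A masked adjudication process in a document not shown would reduce the concern about bias, but the two sections would still need to be tied together.

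**What to change.** 1. Keep the attributable rate. Alongside it, pre-specify a comparison by randomised arm of all Clavien-Dindo grade III–V complications regardless of attribution, from randomisation to the end of the existing adverse event reporting period.
2. Base the conclusion about harms on both results, and discuss any disagreement between them.
3. State which count feeds the cost-effectiveness analysis, and align the wording of Outcome analyses and Economic evaluation, including the grade that defines major in the clinical comparison.

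The cost is wording in the protocol and SAP plus one more analysis. All adverse events are already collected, and recruitment is expected to run to 28 February 2027, so the change can be made before analysis. The drawback is that unrelated events, events before the procedure and possibly interventions for disease progression enter the all-cause count. They add noise and mix some failure of efficacy into the measure of harm, which is why the attributable rate should stay beside it.

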### Randomisation

Participants are randomised by the research team at each site. The individuals at each site who enrol and randomise participants do not have access to the randomised sequence. Randomisation is on a 1:1 basis produced by a computer-generated randomisation via the trial’s online electronic remote data capture (eRDC) system operated by the Cancer Research UK Cancer Clinical Trials Unit (CRCTU), University of Birmingham. Treatment allocation is stratified by the following criteria:

Presence of or intention to insert lumbar drain prior to the protocol-defined intervention.Duration of IIH diagnosis (diagnosis ≤28 days from randomisation or diagnosis >28 days from randomisation).The degree of papilloedema defined by the Frisén grade being <4 or ≥4 in the most affected study eye.

To reduce the risk of any possibility of the treatment allocation becoming predictable, the randomisation algorithm includes a random factor, whereby 80% of randomisations will be ascertained using the minimisation allocation, with the remaining 20% being true randomisation. This approach preserves allocation concealment while maintaining group balance.

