## Discussion

### Justification of trial design

IIH is a rare disease; hence, the numbers to be recruited are relatively small in the context of a phase IIb trial, but similar to other randomised controlled trials in IIH.^2
3
15^ A trial design with repeated measures analyses is, therefore, optimal for this rare disease setting as the models will use data from all time points, thus enabling a smaller sample size while maintaining power to detect a minimum clinically important difference.^41^

Patients will be randomised on a 1:1 ratio of intervention arms to provide an unbiased comparison and to avoid the potential confounding factors implicit in non-randomised comparisons. Randomisation will be minimised based on three key prognostic factors: (1) presence of or intention to insert a CSF lumbar drain prior to the intervention, (2) duration of IIH diagnosis and (3) degree of papilloedema. These factors were identified as prognostic for patient outcomes in a 9-year longitudinal cohort study of 490 patients with IIH.^49^ Baseline imbalances in these variables could influence trial outcomes and interpretation; therefore, minimisation, a dynamic randomisation method that ensures balanced allocation across groups based on selected baseline characteristics, is being used.

In addition to the virtual visit after 18 months of follow-up, two early visits (within the first 6 months) were permitted to be virtual in the updated version of the protocol (V.2.0, dated 7 July 2025). During the first 12 months of the trial being open, the ophthalmology burden on sites was preventing them from approaching patients for inclusion. Therefore, to ease this, sites were allocated two of a potential three visits (at months 2, 3 or 4). Sites are stratified by anticipated number of participants to be recruited to maintain an even distribution of in-clinic and virtual visits across these three time points. It is not expected that a site performs ophthalmology assessments during the virtual visits, and only a streamlined selection of the quality-of-life questionnaires are required.

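### As described, the complication test and the headache models omit the three minimisation factors; if those factors predict these outcomes, both comparisons are mildly conservative

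*Protocol article*

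**What the plan says.** The Randomisation section of the protocol article describes 1:1 allocation in which "80% of randomisations will be ascertained using the minimisation allocation, with the remaining 20% being true randomisation". The factors are lumbar drain (present or intended), diagnosis within or beyond 28 days of randomisation, and Frisén grade below 4 or at least 4 in the worse study eye. The Discussion (Justification of trial design) gives the reason: "These factors were identified as prognostic for patient outcomes in a 9-year longitudinal cohort study of 490 patients with IIH", and "Baseline imbalances in these variables could influence trial outcomes and interpretation".

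The Outcome analyses section then treats the outcomes differently:

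- **Primary RNFL model:** it includes "adjustments for covariates (including but not limited to stratification variables". The other visual outcomes are to be handled similarly.
- **Major attributable complications:** the rate in the two arms "will be compared using a two-sample test for a difference in proportions".
- **Headache outcomes, including monthly headache days:** multilevel negative binomial models. "These models will have fixed terms for the mean baseline value, the assessment times and treatment arm", with random intercepts. The likelihood ratio test drops only the treatment term, so both models in it would omit the minimisation factors.

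No reason is given for the difference. The section presents itself as a short account and refers to the SAP for detail.

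**The concern.** Minimisation makes the arms more alike on the chosen factors than simple randomisation would. If a factor predicts the outcome, the arm difference varies less from trial to trial. An analysis that ignores the factor leaves its contribution in the error variance and so does not credit that reduction. In the headache models, whatever the factors explain beyond the baseline value would sit in the participant intercept variance and widen the interval for arm.

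The cost is lost precision. It matters most for complications, where a conservative comparison makes a true difference between arms harder to show with about 40 per arm. Major complications avoided is also the effect measure of the within-trial cost-effectiveness analysis (Economic evaluation section).

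**Working it through.** **Trial size.** The article states no power or sample size for either outcome. The only size available is that of the primary analysis: 66 complete cases, or 33 per arm. Inflating for 16% missing gives 33 / (1 − 0.16) = 39.3, rounded up to 40 per arm. This reproduces the stated 80.

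**Approximation.** Let R² be the share of outcome variance explained by the factors. With a continuous outcome and perfect balance:

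- true size of the nominal 5% unadjusted test = 2[1 − Φ(1.96/√(1 − R²))]
- interval width relative to the adjusted analysis = 1/√(1 − R²)

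| R² (assumed) | 1.96/√(1 − R²) | True size | Excess width |
|---|---|---|---|
| 0 | 1.960 | 5.0% | 0% |
| 0.10 | 2.066 | 3.9% | 5% |
| 0.20 | 2.191 | 2.8% | 12% |
| 0.30 | 2.343 | 1.9% | 20% |

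Complications are binary and 20% of allocations are purely random, so the actual scheme was also simulated.

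**Complications.** 20,000 simulated trials of 80, with 80/20 minimisation on three binary factors. The pooled two-proportion z-test was compared with a linear risk-difference model adjusted for the factors. Assumed inputs are factor prevalences of 0.3, 0.5 and 0.5, the same odds ratio (OR) for each factor, event rates of 14%, 30% and 40%, and a treatment OR of 1/3 for power. The rates fall within the ranges the Introduction reports for shunt complications and revisions (11–71%) and stent revisions (14%). Ranges below are across the three event rates.

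| OR per factor | Unadjusted type I error | Adjusted SE | Power change with adjustment |
|---|---|---|---|
| 1 | 5.1–5.5% | no gain | no gain |
| 1.5 | 4.5–5.4% | about 1% smaller | about −1 to +1 points |
| 2 | 4.2–4.7% | 2–4% smaller | −0.6 to +2.8 points |
| 3 | 3.5–4.3% | 5–8% smaller | +1.6 to +6.6 points |

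The adjusted test stayed at 4.9–5.5% throughout. Monte Carlo error near 5% is 1.96 × √(0.05 × 0.95/20,000) = 0.3 points.

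The two scales can be linked through the SE ratio, since R² is roughly 1 − ratio². At OR 2 the ratios run from 0.978 to 0.963, so R² is about 4–7%. At OR 3 they run from 0.946 to 0.916, so R² is about 11–16%. The 20% and 30% rows of the approximation therefore need larger odds ratios on all three factors at once.

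**Headache.** 3,000 simulated trials under the same allocation. A continuous outcome stands in for the negative binomial model, and R² is what the factors explain beyond the modelled baseline value. The assumed effect for power is 0.63 SD.

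| Residual R² (assumed) | Unadjusted type I error | Adjusted SE | Power change |
|---|---|---|---|
| 0 | 4.9% | no gain | none |
| 0.05 | 4.5% | 2.5% smaller | +0.7 points |
| 0.10 | 3.3% | 5% smaller | +3 points |
| 0.20 | 3.1% | 11% smaller | +5 points |
| 0.30 | 2.2% | 16% smaller | +8 points |

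Monte Carlo error near 5% is 1.96 × √(0.05 × 0.95/3,000) = 0.8 points, so the results agree with the approximation.

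**The case against.** The strongest reply has four parts.

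1. **The SAP may already cover this.** The article is a summary and does not say that its headache term list is complete. This stands as a caution, mainly for headache. It is weaker for complications, where the article names a specific test that has no place for covariates.

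2. **No link to these outcomes is documented.** The cohort is cited for patient outcomes in general. Neither complications nor headache is named, and no effect size is given. Complications attributable to a procedure may have little to do with Frisén grade or time since diagnosis. For headache, the baseline value may absorb much of any factor effect. This stands, and it makes the point conditional.

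3. **The simple test is valid and robust when events are few.** At a 14% rate, 80 × 0.14 gives about 11 events, and a logistic model with arm and three factors would be fragile. This limits the fix for complications. It does not affect the headache models.

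4. **The outcomes are secondary,** no power is claimed for them, and the omission does not inflate false positives. This stands.

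A reader might infer that both analyses are certainly too conservative, or that the complication test runs near a 2% level with intervals 20% too wide. The documents support neither. The first needs prognostic effects that are not reported. The second takes the top of an assumed R² range for a continuous, perfectly balanced outcome, and no simulated complication scenario came close to it. The article's remark about baseline imbalance justifies the allocation method and does not itself commit the secondary analyses to adjustment.

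**Conclusion.** The point holds in conditional form. As described, two analyses ignore the factors used for allocation, while the primary model includes them, and no reason is given. If the factors predict complications or headache, these comparisons are mildly conservative and lose some precision. If not, they lose nothing.

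For complications the loss is nil to small up to an odds ratio of 2 per factor and becomes clear only near 3. For headache it becomes noticeable once the factors explain about 10% of the variance left after baseline adjustment. These sizes rest on assumed prevalences, odds ratios and R², and on a continuous stand-in for the headache model. The reason to act is that the remedy is cheap, not that the stated analyses are invalid.

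**What to change.** **Headache.** Add the three minimisation factors as fixed effects, in both the full and the nested model of the likelihood ratio test.

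**Major complications.** Report a risk difference with a confidence interval adjusted for the three factors, by standardising a logistic model to the trial population and using a penalised fit if events are few. Present it beside the raw proportions and the two-sample test. State in advance that the simple test is retained if the adjusted model is unstable. The check above used a linear risk-difference model, so the behaviour of the logistic version with few events should be confirmed before it is fixed.

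If the SAP already contains these terms, confirming that is enough. If the omission is deliberate, give the reason.

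**Cost.** Wording and a little extra analysis. The factors are recorded at randomisation, so no new data are needed. Recruitment is expected to run to 28 February 2027, which leaves time to settle this before the final analysis. The one real downside is possible instability of the adjusted complication model when events are few.
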